## Abstract

**Background:**

Sedentary behaviour is associated with cardiometabolic diseases amongst office-bound workers, mostly through extended sitting and engaging in low-energy-demanding activities during work hours. The aim of this study is to assess the effectiveness of standing desks and healthy messages on cardiovascular parameters in a cohort of office-based workers and to explore the perceptions of these workers about the suitability of this intervention to lower occupation-related sedentariness.

**Methods/design:**

The protocol will use a mixed-methods study design. Phase 1 of this study is a 12-month, single blinded, randomised controlled trial, which will include baseline, 3-month, 6-month and 12-month post-intervention assessments of plausible cardiometabolic risk biomarkers in office-bound workers at a South African credit and information management company. These biomarkers include anthropometry, sedentary behaviour and physical activity, sleep duration, blood pressure, glucose, glycated haemoglobin (HbA1c), lipid profile and cardiorespiratory fitness. Participants will be randomised into an intervention or control group. The intervention group will be provided with an adjustable sit–stand desk and receive weekly health-promoting messages for the intervention period. Phase 2 will use focus group discussions conducted post-intervention to explore the study participants’ perceptions of the effectiveness of the intervention. Cardiometabolic risk biomarkers and changes in these variables will be compared between the intervention group and the control group at the four time points using descriptive and inferential statistics.

**Discussion:**

Regression analysis will be undertaken to determine the association of cardiometabolic risk biomarkers with cardiometabolic diseases. A thematic content analysis approach will be used to explore emerging themes from focus group discussions.

**Protocol identification:**

Pan African Clinical Trial Registry, PACTR201911656014962.

## Introduction

The global impact of preventable cardiometabolic and non-communicable diseases remains excessively high; however, low- to middle-income countries (LMICs) such as South Africa bear the greatest burden (World Health Organization 2018). Insufficient physical activity is still the main behavioural risk factor driving the increase in preventable diseases in South Africa. The demands on employee productivity are high, resulting in prolonged sedentary behaviour, particularly amongst clerical workers (Clemes et al. 2014a). Sedentary behaviour is defined as ‘awake’ activities with limited energy expenditure, while in a sitting, reclining or lying posture (Tremblay et al. 2017). Continuous time in sedentary activities is associated with increased risk of cardiometabolic diseases and inflammatory markers, independent of moderate-to-vigorous physical activity (Hadgraft et al. 2020). Domains of sedentary behaviour include time spent sedentary during occupation, transport and outside of working hours (Clemes et al. 2014b). Workers in office-bound occupations are at an increased risk of being sedentary for most of the occupation-related domain (Chau et al. 2010). A study demonstrated that employed individuals use motorised transport for an average of 0.63 ± 0.68 h/day (Clemes et al. 2014b). This study demonstrated that participants who sat for more than 80% of the workday had higher sitting times during motorised commuting compared with those who sat for < 58% of the workday (1.07 ± 0.98 hours per day vs. 0.35 ± 0.27 hours per day, respectively; *p* < 0.0001) (Clemes et al. 2014b). The adult working population in high-income countries has been found to accumulate sedentary behaviour whilst at work, during recreational time at home and during travel time (Chau et al. 2010). Compounded by sedentary activities outside of work, this accumulated sedentary behaviour may increase the risk for cardiovascular disease, type 2 diabetes and all-cause mortality beyond certain thresholds, even adjusting for physical activity (Patterson et al. 2018). Even in LMICs, worker productivity is becoming increasingly reliant on technology-based solutions with little need to move from the seated position for any tasks, which encourages sedentary behaviours (Gradidge 2017). The implications include limited employee productivity, mental health concerns, financial strain and increased absenteeism. It is therefore important to address sedentary behaviour in the workplace.

A study in a high income country demonstrated reductions in cardiovascular disease risk amongst obese office workers following an intervention to address high sitting time by introducing sit-stand desks rather than the introduction of more physical activity (Healy et al. 2017). This study was a multicomponent intervention, including organisational, environmental (sit–stand desks) and individual components, and significantly better improvements were observed in glycaemic control and insulin resistance in the long term (12 months) compared with the short term (3 months) (Healy et al. 2017). Other studies have shown that environmental interventions such as sit–stand desks, electric height adjustable workstations and active workstations (treadmill and cycle ergometer workstations) result in lower sitting time and improvements in work-related activities (Edwardson et al. 2018; Shrestha et al. 2018). Healthy messages, different from guidelines, help influence individuals into a feasible behaviour pattern (Latimer et al. 2010). The public and occupational health guidelines to lower sedentary time, for instance, are made more acceptable through appealing messaging, such as ‘move more and sit less during the day’ (Holtermann et al. 2020). Evidence shows that workplace interventions to reduce sedentary behaviour can be facilitated by healthy messaging to improve behaviour modification (Healy et al. 2017; Manini et al. 2015).

Commonly, the messages aim to persuade individuals that physical activity is appealing and achievable. These supplementary messages can take many forms and can be disseminated through a variety of messaging processes.

However, there is still a paucity of evidence on the effect of workplace health programmes to reduce sedentary behaviour (Hadgraft et al. 2020). Thus far, only one LMIC intervention study has demonstrated a drop in sedentary behaviour amongst office workers, by using tailored mobile text messages to interrupt sitting time (Dunning et al. 2018). Messages reminding the study participants in the intervention group to stand up and take regular short walks were sent every 20 min during working hours in the working week, for the duration of the 10-week trial. This pilot study did not show a change in anthropometry and cardiometabolic disease markers. Indeed, there is an urgent need to address the cardiovascular disease risk profile of South African workers (Patel et al. 2013), and the place of employment may offer the opportunity to develop programmes to improve worker health and wellness (Patel et al. 2010; World Health Organization 2018).

The aim of this study is to assess the effectiveness of standing desks and healthy messaging (from the authors) on the risk of cardiovascular disease and sedentary behaviour in a cohort of office-based workers and to explore their perceptions on the effectiveness of this intervention to lower sedentariness in the workplace. This manuscript will provide information on the framework used to answer the intended study aims.

## Methods

### Study design, setting, participants and selection

This study will use a mixed-methods study design. Phase 1 of the study is a 12-month single-blind randomised controlled trial (RCT). Phase 2 will explore participant perceptions of the effectiveness of the intervention in the workplace.

In the first phase, the study participants will be assigned to an intervention group for 12 months or a control group. They will be randomised into one of two groups: (1) the combined standing desk–healthy messages group or (2) the control group.

The randomisation will be conducted by a qualified biostatistician independent from the core research team.

The potential for contamination will be minimised by adhering to various evidence-based approaches (Magill et al. 2019): (1) participants will be randomised by business unit, (2) participants will be requested not to share details of the intervention, (3) researchers will be asked not to share details of the intervention and (4) a sufficient number of research assistants will be recruited, each allocated to a single business unit. The RCT will be single blinded so that the first and second authors (assessors) are blinded to the group allocation of the study participants.

All adult office workers (18–65 years) from a specific credit and information management company based in Johannesburg (South Africa), working at least 50% of the workday at their desk, 5 days per week, will be invited to participate by the human resources analyst concerned with employee health and wellness through email and telephonic invitations. The inclusion criteria include access to telephone or mobile, email and/or internet and a desk or workstation within the setting; the ability to communicate in English; and the ability to walk or stand for at least 10 min. The exclusion criteria include participants who are pregnant, non-ambulatory or have a diagnosed medical or chronic condition that affects their ability to stand for 10 min or more. Furthermore, participants with other contraindications for working in the standing position and participants not working at the study site will also be excluded from the study. The total current staff complement of the company is 300, and all employees are housed in the same building. The building has three floors, with each respective floor subdivided securely by business unit, thus restricting the movements of staff in the setting.

The sample size for phase 1 of the study will be determined based on the available resources and the assumption that at least 60 participants per group, adjusted for drop-out, will provide > 90% power to detect a significant difference (*p* < 0.05) in sedentary behaviour between the groups (O’Connell et al. 2015).

For phase 2, semi-structured focus group discussions, conducted by author 1, author 2 and research assistants, are planned with six groups of participants selected by participation in the intervention; each group will have six to eight participants. The principle of saturation in its purest sense (as in grounded theory methodology) will not be applied (Creswell 2007). However, the authors will apply the principle of saturation in the sense that it is anticipated that the sample size will be adequate to provide sufficiently rich data, and that a greater sample size would not yield a significant amount of new information (Tracy 2010).

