## Intervention

The combined standing desk–healthy messages group (group 1) will be provided with an adjustable sit–stand desk. The desk is designed for placement on top of the participants’ existing workstation, providing the opportunity to transition from sitting to standing without interrupting productivity. Research assistants, qualified in exercise science, biokinetics or physiotherapy, will set up the participants’ workstations in the most appropriate ergonomic position. The correct configuration will therefore be individualised for each study participant. Participants will be visited weekly by the research assistants to examine the set-up, monitor usage and encourage standing-based work. The participants will be asked to break up extended sitting time by accumulating bouts of standing activity, short intermittent bouts of ≥ 10 min initially and then progressing to longer bouts of ≥ 30 min over the course of the intervention (Smith et al. 2017). Regular communication on the benefits of interrupting sitting will be emailed to the participants. The combined standing desk–healthy messages group will also receive health-promoting messages from the authors focussed on lifestyle behaviour modification through email, short message services and telephonic communication once a week during working hours. The participants in the control group (group 2) will continue using their ‘traditional’ workstations as usual.

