#### Body composition

Total body weight (kg) will be measured to the nearest 0.1 kg using a calibrated digital weighing scale (Omron HN-288, Hoofddorp, The Netherlands), and standing height will be measured to the nearest millimetre using a calibrated portable stadiometer (Seca 213, Hamburg, Germany). The participants will wear minimal clothing and will not have shoes on during the measurements. Trained student researchers and author 2 will conduct the measurements. Body mass index (BMI, kg/m^2^) will be calculated and classified as underweight (< 18.5 kg/m^2^), normal weight (≥ 18.5 kg/m^2^ and < 25 kg/m^2^), overweight (≥ 25 kg/m^2^ and < 30 kg/m^2^) or obese (≥ 30 kg/m^2^) (American College of Sports Medicine 2017). Using a flexible, but inelastic, measuring tape, a measurement of the waist circumference will be taken at the narrowest part of the trunk, horizontally, whist the participants are standing with arms at the side, relaxed abdomen and feet together (American College of Sports Medicine 2017). Similarly, the hip circumference measurement will be taken at the widest circumference of the proximal thigh, just under the fold of the gluteus, with feet separated slightly (American College of Sports Medicine 2017). Central obesity is defined as a waist circumference ≥ 80 cm for females or ≥ 94 cm for males (Alberti et al. 2009).

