#### Cardiorespiratory fitness

The Queens College 3-min step test will be used to estimate cardiorespiratory fitness (using maximal oxygen uptake [VO_2max_]). The agreement between this step test and measured VO_2max_ is high (rho = 0.75, *p* < 0.001). The step test uses a 41.3-cm step with a stepping rate of 24 steps/min for men and 22 steps/min for women for a period of 3 min (American College of Sports Medicine 2017). Within 5 s of the participant sitting, a research assistant will measure the post-exercise heart rate (HR). Maximal oxygen uptake (VO_2max_) will be calculated for men (VO_2max_ = 111.33 – [0.42 × HR]) and women (VO_2max_= 65.81 – [0.1847 × HR]).

### Phase 2

All study participants involved in the combined standing desk–healthy messages intervention and who did not drop out of the RCT will be invited to participate in semi-structured focus groups at intervention follow-up to evaluate their perceptions of the intervention – receiving the healthy messages and/or using the standing desks – and their perceptions of the effectiveness of using these interventions in the workplace. Six focus groups are planned, with six to eight participants per group. Given that this intervention group will have approximately 60 participants, and that not all participants will make themselves available for a focus group, the intention to invite all intervention group participants to take part in a focus group accounts for at least a 60% positive response rate. Although the challenges associated with recruitment for focus groups can sometimes make it difficult to stratify focus groups, an attempt will be made to stratify these focus groups based on participants’ responses to phase 1. During the focus group discussions, participants will be asked to comment to facilitators and address extended sitting time whilst working, and to discuss the most suitable methods to improve health in their place of work. The focus groups will be approximately 45 – 60 min in duration.

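### The single-blind statement conflicts with the roles the protocol gives to the authors and research assistants; the exposure shown is estimated VO2max and, through author 2, body measurements

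*Protocol article*

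**What the plan says.** All references are to the protocol article.

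- **Blinding** (Study design, setting, participants and selection): the trial is described as single blind in that "the first and second authors (assessors) are blinded to the group allocation of the study participants". No one else is said to be blinded.
- **Messages** (Intervention): the standing-desk group "will also receive health-promoting messages from the authors focussed on lifestyle behaviour modification", once a week by email, text message and telephone. The control group carries on with its usual workstations. The aim, at the end of the Introduction, also gives the authors as the source of the messages.
- **Research assistants as intervention staff** (Intervention): they configure the workstations, and "Participants will be visited weekly by the research assistants to examine the set-up, monitor usage and encourage standing-based work". Under the contamination safeguards, "a sufficient number of research assistants will be recruited, each allocated to a single business unit".
- **Body measurements** (Body composition): "Trained student researchers and author 2 will conduct the measurements".
- **Step test** (Cardiorespiratory fitness): a research assistant measures heart rate within 5 seconds of the participant sitting down, and VO2max is calculated from it.
- **Outcomes** (Data analysis): changes in BMI and VO2max are among the listed outcome variables.
- **Focus groups**: "conducted by author 1, author 2 and research assistants", with only intervention participants invited (Phase 2). The Abstract places them after the intervention.

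**The concern.** Participants know whether they have a sit–stand desk, so blinding of assessors is the only blinding this trial can have. It rests on two named people. If they write to or telephone only the intervention group, they know who is in it. If staff who deliver the intervention also take an outcome reading, the assessors include people outside the stated blinding.

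At stake is the comparison between groups on outcomes where the assessor can influence the reading. A hand-taken heart rate just after exercise is such a reading, and tape measurements are too. The trial report would also claim a safeguard that the plan, followed as written, does not deliver.

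**Working it through.** The document gives no figure to reproduce. The check sets the role statements side by side and then looks at how sensitive the one calculated outcome is.

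**Step 1: authors 1 and 2.** The design section needs them not to know allocation. The Intervention section has the authors contact one group only, and does not except these two. Both statements can hold only if the senders are other people. The document names author 1 and author 2 individually elsewhere (focus groups, body composition), but here it uses only the collective term. If author 2 is a sender, the unblinded knowledge reaches the body measurements and so BMI, a listed outcome.

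**Step 2: research assistants.** The design section names authors 1 and 2 as the assessors. The step-test section gives the heart rate to a research assistant. The Intervention section has research assistants fit desks and encourage standing. No separate, blinded group of assistants is described. The staff category that delivers the intervention therefore also measures an outcome. This holds whether whole business units are allocated or people are randomised within units, because in either case the assistants see who has a desk.

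**Step 3: confounding of assessor with arm.** This needs two further conditions: that whole business units are allocated, and that an assistant measures in the unit to which they are assigned. The text permits both and states neither outright. If both hold, each assistant's heart-rate readings belong to one arm only.

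**Step 4: sensitivity of VO2max.** From the Cardiorespiratory fitness section:

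- men: VO2max = 111.33 − 0.42 × HR
- women: VO2max = 65.81 − 0.1847 × HR

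The constants cancel in a difference, so a systematic reading error of *d* beats/min shifts the estimate by 0.42*d* or 0.1847*d*, in the opposite direction to the error. The values of *d* are assumptions.

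| Assumed *d* (beats/min) | Men | Women |
|---|---|---|
| 3 | 0.42 × 3 = 1.26 | 0.1847 × 3 = 0.55 |
| 5 | 0.42 × 5 = 2.10 | 0.1847 × 5 = 0.92 |
| 10 | 0.42 × 10 = 4.20 | 0.1847 × 10 = 1.85 |

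The outcome is change in VO2max. An assessor's constant error cancels if the same person reads at baseline and at follow-up. What matters is an error that differs between visits, for example one that appears once the assessor knows the allocation.

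**Step 5: focus groups.** They would unblind authors 1 and 2 for the trial only if held before or alongside the last assessment. The Abstract says post-intervention. The Phase 1 measures describe the last visit as 12 months post-intervention. The order of the two is not fixed.

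**The case against.** **The authors may not mean authors 1 and 2.** The phrase could describe who wrote the messages, or other team members who send them. That is possible, and author roles cannot be seen in the text available. So it is not established that authors 1 and 2 personally telephone participants. What stands is that the text makes no such distinction, and the blinding statement depends on one.

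**Staffing detail belongs in a full protocol.** An article may leave out who measures each outcome. Here, though, the article assigns the roles, and the assignments do not fit the blinding it claims.

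**The main outcomes are not assessor-read.** The sample size rests on sedentary behaviour, which is recorded by accelerometer and questionnaire. Glucose, HbA1c and lipids are read by analysers. This stands and limits the reach of the point.

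A reader might also infer more than the document supports:

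- *That the focus groups breach the blinding.* They follow the intervention, and the plan to stratify them by responses to phase 1 suggests that phase 1 is largely complete by then. Only the order relative to the last assessment is open.
- *That intervention staff measure waist, hip and blood pressure.* The student researchers are not said to be the research assistants, and no one is named for blood pressure. Waist and hip are touched only through author 2.
- *That assessor and arm are completely confounded.* This needs both conditions in step 3 of the working.
- *That 5 beats/min is an expected bias.* It shows how the equations respond and nothing about the size or direction of a real error.

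**Conclusion.** The point holds in a limited form. The single-blind statement cannot stand beside the other role assignments as written.

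The research-assistant part is the firmest: staff who deliver the intervention take the reading that determines VO2max. Strictly, this undercuts the claim of assessor blinding; it does not contradict the words about authors 1 and 2. The message part is a conflict on plain reading, and would disappear if the senders were stated to be other people. The focus groups need only a sentence on timing.

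The demonstrated exposure is estimated VO2max and, if author 2 is among the senders, body measurements including BMI. The bias itself cannot be sized. Assumed reading errors of 3 to 10 beats/min correspond to 1.3 to 4.2 units in men and 0.6 to 1.8 in women.

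**What to change.** 1. Have the messages and calls sent automatically, or by a team member who assesses no outcome, and not by author 1 or 2.
2. Have the step-test heart rate taken by existing staff who do not deliver the intervention to that participant, away from the workstations and without being told the allocation.
3. State that focus groups led by authors 1 and 2 start only after the last trial assessment.
4. Where any of this cannot be done, restrict the single-blind claim to the outcomes it covers and report the others, including VO2max, as assessed unblinded.

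The cost is reassignment of roles and some rescheduling. If assistants cross units in assessment weeks, the safeguard of one unit per assistant is slightly loosened. Assistants who work in the same building may also guess which units have desks, so item 2 may not conceal allocation fully. Item 4 alone needs only a change of text, but it corrects the claim and leaves the risk of bias as it is.

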## Data analysis

All data for the RCT will be analysed using Stata Special Edition (SE) (version 14, Stata Corp, United States of America). Descriptive statistics will be used for comparing outcome data at baseline and change from baseline to follow-up between the intervention and control groups. Paired *t*-tests for within-group comparisons over time or their non-parametric equivalents depending on data distribution will be utilised. Comparison between groups will be made using analysis of variance or the non-parametric equivalent. Multivariable linear regression models will be used to determine if any of baseline study variables modulate these effects on the outcome variables (change in BMI, lipids, BP, HbA1c, VO_2max_ and sedentary behaviour). Significance will be accepted at an alpha level of *p* ≤ 0.05. The Consolidated Criteria for Reporting Qualitative Research (COREq) checklist will be used for reporting on the methodology, research team, study design and analysis, and study findings (Tong et al. 2007).

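### The > 90% power stated for 60 per group shows no allowance for randomisation by business unit, so it is unsupported for this design

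*Protocol article*

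**What the plan says.** All of the design statements are in the protocol article, under Study design, setting, participants and selection.

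- **Size and power.** The number for phase 1 rests on resources and on an assumption, supported by a citation, that "at least 60 participants per group, adjusted for drop-out, will provide > 90% power to detect a significant difference". The outcome is named only as a difference "in sedentary behaviour between the groups".
- **Randomisation.** First in the list of steps to limit contamination is that "participants will be randomised by business unit". In the same list, each research assistant is assigned to one unit only.
- **Setting.** The company has 300 staff in one building. "The building has three floors, with each respective floor subdivided securely by business unit", which restricts staff movement. The number of units is not given.
- **Analysis.** The Data analysis section compares groups by analysis of variance or a non-parametric equivalent, and uses multivariable linear regression to look at baseline modifiers. "Significance will be accepted at an alpha level of *p* ≤ 0.05". No term for business unit appears in any of these methods.

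**The concern.** Power depends on the unit of randomisation. If whole business units are allocated, colleagues in a unit share a manager, a work pattern and, here, a single research assistant. In the intervention arm that assistant visits weekly and encourages standing (Intervention section). Outcomes within a unit are then likely to be correlated. Sixty people in a few units carry less information than 60 independent people, and the reference distribution for the group comparison depends on the number of units rather than the number of people.

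The article puts a definite power figure beside a definite randomisation method, and nothing in the figure or the analysis connects the two. This is the only quantitative justification of the trial's size. If the outcome analysis shows no difference, readers will weigh that result against a claim of more than 90% power. If the claim ignores clustering, they will give the null result too much weight.

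**Working it through.** **Inputs from the article.** 60 per group, power above 90%, significance level 0.05, allocation by business unit, 300 staff on three floors.

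**Inputs assumed, because the article gives none.** Two-sided test; ICC 0.01 to 0.10; 3, 6 or 10 equal-sized units per arm (6, 12 or 20 in total, hence 20, 10 or 6 participants per unit); a standardised difference d to be varied.

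**Step 1: the plan's own figure.** It cannot be reproduced directly because no difference or SD is shown. It can be solved backwards under independence:

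d = (1.960 + 1.282) × √(2/60) = 3.242 × 0.1826 = 0.592

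The noncentral t solution with 118 df is 0.597. Power at 60 per group for other values of d (normal approximation) is 38% at 0.3, 59% at 0.4, 78% at 0.5, 91% at 0.6 and 99% at 0.8. So even without clustering the claim needs a planned difference of about 0.6 SD or more.

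**Step 2: add clustering at d = 0.592.** With m participants per unit and k units per arm:

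- design effect DE = 1 + (m − 1) × ICC
- effective number per arm = 60 / DE
- power from the normal approximation (design effect alone), then from a noncentral t with 2k − 2 df (cluster-level)

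Worked example, 6 units per arm, ICC 0.05: DE = 1 + 9 × 0.05 = 1.45; effective n = 60 / 1.45 = 41.4; noncentrality = 0.592 × √(41.4/2) = 2.69; power 77%, or 68% with 10 df.

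| Units per arm (m) | ICC | DE | Effective n per arm | Power, design effect alone | Power, 2k − 2 df |
|---|---|---|---|---|---|
| 10 (6) | 0.01 | 1.05 | 57.1 | 89% | 85% |
| 10 (6) | 0.05 | 1.25 | 48.0 | 83% | 78% |
| 10 (6) | 0.10 | 1.50 | 40.0 | 75% | 71% |
| 6 (10) | 0.01 | 1.09 | 55.0 | 87% | 80% |
| 6 (10) | 0.05 | 1.45 | 41.4 | 77% | 68% |
| 6 (10) | 0.10 | 1.90 | 31.6 | 65% | 57% |
| 3 (20) | 0.01 | 1.19 | 50.4 | 84% | 61% |
| 3 (20) | 0.05 | 1.95 | 30.8 | 64% | 43% |
| 3 (20) | 0.10 | 2.90 | 20.7 | 48% | 31% |

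Every row is below 90%.

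**Step 3: the detectable difference.** Before any loss of degrees of freedom, the difference detectable with 90% power is 0.592 × √DE. At ICC 0.05 that is 0.66 SD (10 units per arm), 0.71 SD (6 per arm) and 0.83 SD (3 per arm).

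**Step 4: could a larger planned effect rescue the claim?** Sometimes.

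| d | Units per arm | ICC | Power, design effect alone | Power, 2k − 2 df |
|---|---|---|---|---|
| 0.8 | 10 | 0.10 | 95% | 92% |
| 0.8 | 6 | 0.05 | 95% | 90.5% |
| 0.8 | 6 | 0.10 | 89% | 82% |
| 0.8 | 3 | 0.05 | 88% | 66% |
| 1.0 | 6 | 0.10 | 98% | 95% |
| 1.0 | 3 | 0.05 | 97.5% | 83% |

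**The case against.** Several points on the other side have force.

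**The shortfall is conditional.** Fixing d at the value that gives exactly 90% under independence guarantees that any design effect pushes power below 90%. The article claims more than 90% and does not disclose d. Step 4 shows clustered designs in which the claim survives. A reader might infer that the trial fails to reach 90% power, or that its true power is some particular middling figure. The document supports neither, because the effect, the ICC and the number of units are all unknown.

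**Independence is not stated.** A reader might also infer that the calculation assumed independent participants. The article does not say so, and the source it cites is not available here. What can be said is that no allowance for clustering is shown.

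**The randomisation phrase could mean stratification.** The section also speaks of participants being randomised into one of two groups. With individual allocation stratified by unit, this loss of power would not arise. But that would seat both arms together within a unit and defeat the stated purpose of limiting contamination, so the cluster reading is the more natural one.

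**A journal article condenses.** The absence of an SD, an effect size or a drop-out rate is not a finding in itself, and none is claimed. Nor does the drop-out wording carry weight. It can be read as 60 enrolled or 60 remaining, but the article says an allowance was made, and the Phase 2 text uses about 60 as its base for focus-group invitations.

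**The study calls its output formative**, and its size is also limited by resources. That softens the consequence. It does not make an unqualified power figure fit a different design.

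**Conclusion.** The concern holds in this form: the statement that 60 per group "will provide > 90% power to detect a significant difference" is unsupported for a trial that allocates by business unit, because neither the power statement nor the planned analysis shows any allowance for clustering.

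The size of the problem depends on what lies behind the number 60. If it was sized for about 90% with independent participants, power under unit randomisation is below 90% for any positive ICC: about 48% to 89% from the design effect alone and about 31% to 85% with cluster-level degrees of freedom, over the assumed range in Step 2. If the planned effect was larger, for example 0.8 SD with at least 12 units in total and an ICC up to 0.05, the claim can stand. The document does not allow a choice between these cases. The conclusion rests on the cluster reading of the randomisation phrase and on equal-sized units.

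**What to change.** Replace the unqualified power figure with a short paragraph that:

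- states plainly that business units are the units of randomisation (or, if allocation is individual within units, says so) and gives their number per arm;
- names the sedentary measure (accelerometer or questionnaire) and the time point to which the power refers;
- gives power, or the minimum detectable difference, using the actual number of units, an ICC range such as 0.01 to 0.10, and the expected number of completers;
- shows the assumed difference and SD;
- bases the calculation on an analysis that accounts for business unit, and amends the Data analysis section to match.

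The cost is a recalculated paragraph, a matching line in the analysis section, and probably a less favourable stated figure. No extra enrolment is needed. If the original figure survives the calculation, the paragraph will show it.
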